### Outcomes

#### Primary outcome

The primary outcome is the conversion to AD dementia within 3 years of follow-up after the diagnosis of MCI. Visits to assess the study outcome are planned every 6 months. Follow-up time starts at the date of neuropsychological evaluation at baseline and ends at (i) date of conversion, (ii) end of follow-up, (iii) death and (iv) loss to follow-up, whichever occurs first. The conversion to dementia will be diagnosed by specialists according to the American Psychiatric Association’s Diagnostic and Statistical Manual of Mental Disorders, Fifth Edition (DSM-5) on the basis of clinical, cognitive and functional examination, including the CDR. The diagnosis will not be performed based on any of the biomarkers under study as clinicians are blinded with respect to the biomarkers evaluation which is a necessary condition to correctly evaluate the predictive performance of biomarkers and avoid biased estimation of the association between predictors and outcome. Conversion to Alzheimer’s disease is confirmed when an individual receives two consecutive diagnoses of the same type. The date of the first diagnosis will be considered as the date of conversion.

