#### Secondary outcome

The secondary outcomes are the conversion to Alzheimer’s disease within 3 years of follow-up in amnesic patients and the conversion to other forms of dementia.

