For CSF biomarkers, p-tau, t-tau, Aβ1-42, Aβ_1-42/1–40_ ratio and Aβ_1-42_ /p-tau ratio will be evaluated separately. The cut-offs used for each biomarker are reported in Table 3 along with the literature references [28–31]. For the EEG, the classification of results into normal or abnormal based on the SW values will be performed by the expert centre using a machine learning (ML) method based on fine Gaussian support vector machine. This ML classification model has been trained on external data including both healthy individuals and individuals with AD [32] and will be applied to the study cohort. The FDG-PET result will be categorised as either positive or negative by the evaluators at the expert centre based on the methodology previously described [10, 11]. In the case of FDG-PET positivity, it will also be specified whether it is indicative of an AD-like form or other forms of dementia. The APOE-e4 genotype will be classified as none, one (heterozygosis), or both alleles (homozygosis) (see Table 3 and Additional file 3 for details of the cut-offs and literature references).

**Table 3 Tab3:** Reference value for identifying abnormal values by biomarkers

Biomarker	Reference value for categorisation	Literature and notes
**MMSE**	Age- and sex-adjusted score < 24	Applied correction factors from Measso et al. [26] for age ≤ 64 and Magni et al. [25] for age > 64
**DFR**	Age-adjusted score ≤ 6.31	Frasson et al. 2011 [27]
**Hippocampal volume**	< 5° percentile of the normative population	De Francesco et al. 2021 [12]; see Additional file 3

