**CSF biomarkers**		
Aβ (1–42)	≤ 640 pg/ml	Bellomo et al. 2021 [28]
Total-tau	≥ 404 pg/ml	Bellomo et al. 2020 [29]
Phosphorylated Tau 181 (p-Tau)	≥ 56 pg/ml	Bellomo et al. 2020 [29]
Ratio Aβ_1-42/1–40_	≤ 0.068	Doecke et al. 2018 [30], Leitão et al. 2019 [31]
**Ratio** Aβ_1-42 /p-Tau_	≤ 11.8	Leitão et al. 2019 [31]
**EEG**	Classified in physiological vs pathological based on Small World for the seven EEG frequency bands using machine learning technique	Vecchio et al. 2023 [32]
**FDG-PET**	Classified in negative and positive (AD-like, other forms) using the optimised SPM procedure	Della Rosa et al. 2014 [10], Perani et al. 2014 [11]
**APOE- e4**	Classified in none, one allele, both the alleles	

However, these cut-offs were determined to discriminate between normal cognition and AD, but the population under study is at higher risk of developing dementia compared to the normal population. Therefore, for continuous biomarkers the receiver operating characteristic (ROC) curves will be used to identify new optimal cut-offs for the specific population under study. For biomarkers known to be influenced by sex and/or age, the corrected values will be used. In this context, sensitivity and specificity are both considered targets for determining the optimal cut-off; therefore, among all the commonly used methods [33], the distance to the left-upper corner was chosen. This method maximises both sensitivity and specificity and guarantees a better balance between the two measures [34]. Warnings are raised about its use as not always the method leads to an optimal cut-off in the intention of maximising overall correct classification rates compared to the commonly used Youden’s method [35]; therefore, Youden’s method will be also provided for comparison.

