#### Predictive performance

For each biomarker in the categorical form, the accuracy measures (sensitivity, specificity, positive predictive value, negative predictive value, overall accuracy, positive and negative likelihood ratios) will be calculated for comparison with the literature. For continuous biomarkers, the area under the receiver operating characteristic curve (AUC) will be also reported. Moreover, a univariate analysis will be conducted using the proportional hazard Cox model.

To evaluate the performance of the prediction models, several measures will be considered. The concordance c-index with its 95% CI will be provided as a discrimination measure and the extensions of binary AUC to survival analysis proposed by Harrell will be used [40, 41]. The Akaike information criterion will be provided as a measure of the goodness of fit of the model.

The added value on performance of each biomarker to the multivariable model with demographical and clinical variables will be assessed by the category-free Net Reclassification Improvement (NRI), which is the net proportion of events reclassified correctly plus the net proportion of non-events reclassified correctly. The delta AUC (difference in c-statistics) will be also provided [41], and the likelihood ratio test will be used to assess the statistical significance of the incremental contribution of each biomarker [36, 37].

In addition, to assess the predictive performance of the final multivariable model, calibration measures will also be reported [38, 42]. A calibration plot will be done by plotting the observed outcome proportion (on the *y*-axis) versus the ordered predicted outcome probabilities (on the *y*-axis) by quantile of the predicted risk. Subsequently, the calibration intercept and slope and their 95% CI will be estimated. There is a perfect calibration when the intercept is zero and the slope is one. Moreover, overall measures of performance, the Nagelkerke’s *R*^2^ and the Brier score, will be provided. The Brier score is a composite measure of discrimination and calibration with lower scores indicating improved model accuracy, and it will be calculated at a fixed time point (3 years).

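### FDG-PET is defined as positive for any dementia pattern while the primary outcome is AD dementia only, and the plan does not say how the recorded AD-like / other-forms subtype is used

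*SAP article*

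**What the plan says.** Under Statistical analysis method the SAP article first gives FDG-PET two levels: "The FDG-PET result will be categorised as either positive or negative by the evaluators at the expert centre". The next sentence adds a subtype: "In the case of FDG-PET positivity, it will also be specified whether it is indicative of an AD-like form or other forms of dementia". Table 3 has the same structure: "Classified in negative and positive (AD-like, other forms) using the optimised SPM procedure".

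The outcome that the test is judged against is narrower. Under Primary outcome: "The primary outcome is the conversion to AD dementia within 3 years of follow-up after the diagnosis of MCI". Other dementias appear only under Secondary outcome, which lists "the conversion to Alzheimer’s disease within 3 years of follow-up in amnesic patients and the conversion to other forms of dementia".

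Predictive performance then asks for two-by-two summaries: "For each biomarker in the categorical form, the accuracy measures (sensitivity, specificity, positive predictive value", together with negative predictive value, overall accuracy and likelihood ratios. Statistical model and variable selection makes all biomarkers eligible for the Cox model and stepwise selection but names no PET coding. Analysis of secondary clinical endpoints repeats the univariate analysis and applies the primary model. It gives no separate PET coding for the other-dementia outcome.

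**The concern.** Sensitivity, specificity, PPV and likelihood ratios need a two-level test. The only two-level PET result that the plan defines is positive against negative, and positive includes patterns that point away from AD. Taken as written, a patient whose scan suggests a non-AD dementia, and who indeed does not convert to AD, counts against PET as a false positive.

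The study's aim is to find which biomarker or set of biomarkers predicts AD conversion, and PET is the only one listed with an explicit AD versus non-AD reading. Its coding feeds the accuracy table, the hazard ratio, the NRI and delta AUC, and eligibility in the stepwise procedure. The section on risk groups also holds that avoiding treatment of a false positive matters as much as treating a true positive. If the coding is left open, it can be chosen after the data are seen.

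**Working it through.** **The plan's own figures.** The document gives no PET accuracy figure. The nearest stated figures are the Table 2 half-widths for N = 400. For specificity the formula is 1.96 × √[Sp(1 − Sp) / (N(1 − p))]. With Sp = 0.80:

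- p = 0.27: 1.96 × √(0.16/292) = 4.6 points
- p = 0.35: 1.96 × √(0.16/260) = 4.9 points
- p = 0.40: 1.96 × √(0.16/240) = 5.1 points

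These match Table 2, as do its other cells to within rounding.

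**Inputs for the coding effect.**

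- From the document: N = 400 and AD incidence p of 27% to 40% (Sample size and Table 2).
- Assumed: AD-like-only coding has sensitivity Se = 75% and specificity Sp = 80%.
- Assumed: f is the share of AD non-converters with an other-form scan, taken as 5, 10 and 20%.
- Assumed: a is the share of AD converters with an other-form scan, taken as 0 and 5%.

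**Formulas under any-positive coding.**

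- Sensitivity = Se + a, so it stays the same or rises.
- Specificity = Sp − f.
- LR+ = (Se + a) / (1 − Sp + f).
- PPV = p(Se + a) / [p(Se + a) + (1 − p)(1 − Sp + f)].
- NPV = (1 − p)(Sp − f) / [(1 − p)(Sp − f) + p(1 − Se − a)].

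PPV and LR+ fall exactly when a/f < Se/(1 − Sp), that is, when other-form scans are less predictive of AD than AD-like scans. Here the limit is 0.75/0.20 = 3.75. NPV rises when a/f > (1 − Se)/Sp = 0.25/0.80 = 0.31 and falls when it is below that.

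**Results at p = 40%** (160 converters, 240 non-converters):

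| Coding | f | a | Sens | Spec | LR+ | PPV | NPV | False positives |
|---|---|---|---|---|---|---|---|---|
| AD-like only | – | – | 75% | 80% | 3.75 | 71.4% | 82.8% | 48 |
| Any positive | 5% | 0 | 75% | 75% | 3.00 | 66.7% | 81.8% | 60 |
| Any positive | 10% | 0 | 75% | 70% | 2.50 | 62.5% | 80.8% | 72 |
| Any positive | 20% | 0 | 75% | 60% | 1.88 | 55.6% | 78.3% | 96 |
| Any positive | 5% | 5% | 80% | 75% | 3.20 | 68.1% | 84.9% | 60 |
| Any positive | 10% | 5% | 80% | 70% | 2.67 | 64.0% | 84.0% | 72 |
| Any positive | 20% | 5% | 80% | 60% | 2.00 | 57.1% | 81.8% | 96 |

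Worked example for f = 10%, a = 0: PPV = 0.4 × 0.75 / (0.4 × 0.75 + 0.6 × 0.30) = 0.300/0.480 = 62.5%, and false positives = 240 × 0.30 = 72.

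**At p = 27%, a = 0:** PPV is 0.2025/(0.2025 + 0.73 × 0.20) = 58.1% under AD-like-only coding. For f = 5, 10 and 20% it becomes 52.6%, 48.0% and 41.0%.

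A loss of 5 points in specificity is about one Table 2 half-width.

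**The case against.** A reader might infer that the plan has fixed PET as any-positive throughout, so that its specificity and predictive value are understated and it may be dropped by stepwise selection. The document does not support that much.

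- The subtype is recorded for every positive scan and appears in Table 3's categorisation column, so AD-like-only or three-level coding remains compatible with the text.
- No section says that a pooled PET term enters the Cox model. Loss of rank or removal by stepwise selection cannot be calculated from what is given.
- APOE is listed with three levels and no two-way split, so the request for accuracy measures does not by itself settle how a multi-level marker is split.
- Additional file 3, cited for cut-off details, is not shown.
- Predictive value is too broad a term, since NPV can rise under pooling.
- Any-positive specificity would be a correct figure for a different index test, not a biased estimate.
- The PET accuracy and f used above are assumptions. If f is small, the effect is lost within the sampling error.
- Conversion is a clinical diagnosis made blind to the biomarkers. Some AD converters may therefore have other-form scans, and AD-like-only coding would miss them.

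All of this limits the size and certainty of the point. It does not remove it. The only two-level PET result stated in the text puts other-form scans on the positive side. The APOE entry also shows that the plan spells out three levels where it means them. Neither the accuracy measures nor the models are told to use the subtype.

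**Conclusion.** The point holds conditionally. As worded, the PET binary does not match the AD-only primary outcome, and the use of the subtype is not stated. If the binary is used for the accuracy measures, specificity is lower by f, and PPV and LR+ are lower under the condition shown. Sensitivity does not fall, and the direction for NPV is not determined.

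The size depends on f, which the document does not give. Over the assumed range of 5 to 20%, with a = 0 and 40% incidence, specificity drops by 5 to 20 points and PPV by about 5 to 16 points (71.4 − 66.7 and 71.4 − 55.6).

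For the Cox model the finding is that the coding is not fixed. A pooled term would average patterns expected to carry different AD risk, but the plan does not say that it will use one.

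**What to change.** State the following in Statistical analysis method and Table 3:

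- For the AD outcome, the accuracy measures count AD-like scans as test-positive, and other-form and negative scans together as test-negative.
- In the Cox and stepwise models, PET enters either as three levels (negative, AD-like, other forms) or as the AD-like indicator, with the choice made now.
- For conversion to other dementias, other-form scans are test-positive.
- Any-positive versus negative is reported as a supplementary result, which keeps comparison with the literature possible.

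The subtype is already to be recorded, so this is a change of wording only. Three levels cost one extra parameter against the stated allowance of up to 17 candidate predictors, and the AD-like indicator costs none. AD-like-only coding may lose some sensitivity if AD converters have other-form scans. The supplementary any-positive result would show how much.

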**CSF biomarkers**		
Aβ (1–42)	≤ 640 pg/ml	Bellomo et al. 2021 [28]
Total-tau	≥ 404 pg/ml	Bellomo et al. 2020 [29]
Phosphorylated Tau 181 (p-Tau)	≥ 56 pg/ml	Bellomo et al. 2020 [29]
Ratio Aβ_1-42/1–40_	≤ 0.068	Doecke et al. 2018 [30], Leitão et al. 2019 [31]
**Ratio** Aβ_1-42 /p-Tau_	≤ 11.8	Leitão et al. 2019 [31]
**EEG**	Classified in physiological vs pathological based on Small World for the seven EEG frequency bands using machine learning technique	Vecchio et al. 2023 [32]
**FDG-PET**	Classified in negative and positive (AD-like, other forms) using the optimised SPM procedure	Della Rosa et al. 2014 [10], Perani et al. 2014 [11]
**APOE- e4**	Classified in none, one allele, both the alleles	

However, these cut-offs were determined to discriminate between normal cognition and AD, but the population under study is at higher risk of developing dementia compared to the normal population. Therefore, for continuous biomarkers the receiver operating characteristic (ROC) curves will be used to identify new optimal cut-offs for the specific population under study. For biomarkers known to be influenced by sex and/or age, the corrected values will be used. In this context, sensitivity and specificity are both considered targets for determining the optimal cut-off; therefore, among all the commonly used methods [33], the distance to the left-upper corner was chosen. This method maximises both sensitivity and specificity and guarantees a better balance between the two measures [34]. Warnings are raised about its use as not always the method leads to an optimal cut-off in the intention of maximising overall correct classification rates compared to the commonly used Youden’s method [35]; therefore, Youden’s method will be also provided for comparison.

#### Statistical model and variable selection

Initially, an analysis of socio-demographic and clinical variables will be conducted using the Cox model to identify a core of variables significantly associated with the outcome that will be included in the development of the prognostic multivariable model. A check of multicollinearity between predictors will be assessed, then a stepwise selection starting from the full model will be applied using a threshold of 0.10 for removal and 0.05 for re-admission of variables. A final check of variables not selected by stepwise will be conducted using the likelihood ratio test [36, 37]. Age and sex will be forced in the procedure selection and retained in the final model. Subsequently, these selected variables will be included in multivariable models with the addition of individual biomarkers one at a time. The additional predictive value of each biomarker beyond clinical and socio-demographic variables will be calculated. The performance results will be used to determine for each biomarker which form (continuous or categorical) will be chosen for the development of the multivariable prediction model. Categorisation is typically preferred for the application in clinical practice, but as any categorisation implies a loss of information, we will select the biomarker in a categorical form if the loss in performance could be considered negligible with respect to the continuous form. Categorisation will also be chosen in cases where non-linearity is detected for the continuous form. The categorisation according to the threshold provided by the experts (Table 3) will be preferred in case a small loss of performance is observed compared to the continuous form.

The final predictive model will be identified through a multivariable model considering as eligible predictors all the biomarkers and all selected predictors among the clinical and socio-demographic variables using the stepwise selection procedure as described above. Age and sex will be forced into the model selection process. A final check of the result from the automatic selection procedure will be conducted to ensure that no significant biomarkers were excluded and, vice versa, that no negligible biomarkers were included.

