### Study objectives

The primary aim of the study is to develop and internally validate a multivariable prediction model capable of identifying a biomarker or a set of biomarkers to predict the conversion from MCI to Alzheimer’s disease after 3 years of follow-up.

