### Statistical analysis method

All the analysis will be conducted on patients with the baseline assessment of biomarkers available; consequently, patients without biomarker assessment will be excluded from the primary analysis.

To exclude selection bias, a comparison of baseline characteristics of individuals not included in the analysis due to incomplete biomarkers assessment and those included in the analysis will be performed.

A multivariable predictive model of conversion to AD will be developed including biomarkers, socio-demographic and clinical predictors. The evaluation of biomarkers for MMSE, DFR, CSF parameters and MRI measures will be conducted considering the continuous form and the categorical form applying validated cut-offs.

For the MMSE [24], a cut-off of 24 (< 24) for the age- and sex-corrected score will be used, as indicated in the literature [25]. For the correction of the crude score, Measso et al. [26] will be used for individuals aged ≤ 64, and Magni et al. [25] will be used for those aged > 64. Regarding the DFR, a test result will be classified as abnormal if the age-adjusted score is ≤ 6.31 [27].

For MRI, measurements of the right and left hippocampus are considered for each technique, ACM-Adaboost and Freesurfer, and atrophy is defined below the 5th percentile according to the age-specific thresholds defined for individuals aged 56–90 years, as published [12]. For individuals aged 50–55 years, the cut-offs are extrapolated from the 5th percentile function (see Additional file 2). Right and left hippocampal atrophy measured with the two techniques will be analysed separately.

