### Model presentation and risk groups

For each predictive model, the hazard ratios with 95%CI and *p*-value will be reported. For the final predictive model, a nomogram will be generated. A nomogram is a graphical representation of the statistical predictive model. It is a visual tool that translates model numeric results into a visual format, making it easier to estimate an outcome based on multiple variables. Each variable occurrence is assigned a specific score based on its contribution to the overall prediction. The total score from all variables is then used to estimate the probability of the predicted event (in this case, the conversion to AD at 3 years) conditioning to the individual characteristics [45]. For this purpose, the covariates in the Cox model will be centred. Sensitivity and specificity corresponding to different thresholds of the prediction risk score will also be provided for the final model. Finally, three or more risk categories will be proposed defining low-, medium- and high-risk groups based on the predictive risk score considering the highest sensitivity corresponding to an adequate level of specificity. This category definition will help the clinician with the choice to treat individuals with MCI based on the likelihood of converting to dementia in the following 3 years. Because avoiding the clinical consequence of treating a false positive is a target as important as treating a true positive, a rate of false positives less than 20% (i.e. specificity of at least 80%) is considered acceptable for a medium–high-risk group. We will start by inspecting deciles of the predictive score and grouping them into homogeneous classes based on levels of sensitivity and specificity. Kaplan–Meier curves will be presented for each risk group.

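### The stepwise rule that names the predictive biomarkers does not limit false inclusion across the set, so selection alone is weak evidence for any one biomarker

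*SAP article*

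**What the plan says.** Study objectives asks for a multivariable model "capable of identifying a biomarker or a set of biomarkers to predict the conversion from MCI" to Alzheimer's disease. Naming the biomarkers is therefore part of the primary aim, alongside prediction.

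Statistical model and variable selection gives the rule: "a stepwise selection starting from the full model will be applied using a threshold of 0.10 for removal and 0.05 for re-admission of variables". The final model applies it "considering as eligible predictors all the biomarkers and all selected predictors among the clinical and socio-demographic variables using the stepwise selection procedure", with age and sex forced. A last check is meant to catch significant biomarkers left out and negligible ones left in, but no criterion is given for either.

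Statistical analysis method lists several measures within two modalities: "Right and left hippocampal atrophy measured with the two techniques will be analysed separately", and "For CSF biomarkers, p-tau, t-tau, Aβ1-42, Aβ_1-42/1–40_ ratio and Aβ_1-42_ /p-tau ratio will be evaluated separately".

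Other sections bear on the point:
- **Predictive performance:** a likelihood ratio test, a change in c-statistic and a net reclassification index for each biomarker added singly to the clinical model. No joint test or multiplicity rule is stated.
- **Internal validation:** 500 bootstrap samples with selection repeated in each. The stated outputs are a corrected c-index, corrected calibration and shrunken coefficients.
- **Sensitivity analysis:** selection repeated at other p levels, at the AIC level (0.157) and by LASSO, to examine robustness of selection. The only comparison stated is of predictive performance.
- **Model presentation and risk groups:** "For each predictive model, the hazard ratios with 95%CI and" p-values are reported, with no note that selection came first.

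**The concern.** Each biomarker is judged by its own p-value against 0.10, in a search that starts from all of them. The chance that at least one uninformative biomarker ends up in the named set therefore grows with the number of candidates, and the plan neither limits nor reports it.

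The corrected c-index will not reveal the problem, because an uninformative term hardly changes it. The p-values printed for the final model will not reveal it either: a null p-value that has survived a 0.10 cut is below 0.05 about half the time.

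The introduction says the findings will be used to identify individuals eligible for disease-modifying treatment, and some candidates need a lumbar puncture or a PET scan. Which biomarkers belong in the set is thus a conclusion of the study in its own right, separate from how well the model predicts.

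**Working it through.** **Inputs from the document.** Removal at 0.10 and re-admission at 0.05; all biomarkers eligible; age and sex forced; 400 evaluable people; 40% conversion at 3 years (Sample size).

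**Number of candidates.** The plan gives no total. There are seven modalities: MMSE, DFR, CSF, FDG-PET, MRI, EEG and APOE. Counting the separate measures gives MMSE 1 + DFR 1 + CSF 5 + MRI 4 (two sides, two techniques) + EEG 1 + PET 1 + APOE 1 = 14 variables. I use 7 and 14 as the two ends.

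**The plan's own figures first.** With the Riley shrinkage criterion at S = 0.9 (assumed) and R² = 0.31:
- people per parameter = 1/[(0.9 − 1)·ln(1 − 0.31/0.9)] = 23.68
- events per parameter = 23.68 × 0.16 × 2.5 = 9.47 (stated 9.5)
- parameters at 400 people = 400/23.68 = 16.9 (stated 17)

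These reproduce. The plan states no false-selection rate to compare with.

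**False inclusion of one null biomarker.** The nominal rate is 10%. Stepwise selection was simulated with no biomarker effect, using Cox fits (N = 400, about 150 events, age and sex forced) and a quadratic approximation to the likelihood. The mean number selected was 0.69-0.71 of 7 and 1.33-1.94 of 14. Dividing, 0.69/7 = 9.8% and 1.94/14 = 13.9%, so about 10-14% per biomarker. The higher values come from correlated CSF and hippocampal measures.

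**At least one useless biomarker when three are truly predictive.** This is the case closest to what the plan expects. Under independence the rate is 1 − 0.9^m for m null terms:
- 7 terms, m = 4: 1 − 0.9^4 = 34%
- 14 terms, m = 11: 1 − 0.9^11 = 69%

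Cox stepwise simulations assumed log hazard ratios of 0.4-0.5 for continuous markers and 0.8 for a binary one:

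| Setting | 7 terms | 14 terms |
|---|---|---|
| N = 400, 400 runs | 38% | 68% |
| N = 400, 200 runs (about ±7 points) | 36% | 76% |
| N = 320, 200 runs (illustrative, since the 500 target was missed) | 39% | 79% |

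Of the falsely kept biomarkers, 49-60% had p < 0.05 in the final model.

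**At least one biomarker when none has any effect.** By formula, 1 − 0.9^7 = 52% and 1 − 0.9^14 = 77%. Simulations gave 48-54% for 7 terms and 76-81% for 14. At the AIC level used as a sensitivity analysis, 1 − (1 − 0.157)^14 = 91%.

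**Not simulated.** ROC-derived cut-offs and the performance-based choice between continuous and categorical form were left out. Both give a null biomarker further chances to look useful.

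**The case against.** This is a prediction-model plan, and strict error control over candidate predictors is not a standard requirement there. Noise terms mainly cause overfitting. The plan deals with that by repeating selection in the bootstrap, correcting performance and shrinking coefficients. It also tests each biomarker over the clinical model, checks collinearity, tries LASSO and names the lack of external validation as a major limitation. All of this stands, and it is why the nomogram can be kept. It does not answer the other half of the aim, since none of these outputs says how reliably a given biomarker is selected.

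The case with no effect at all is not what the plan expects. Its biomarkers were chosen on published accuracy, and the model is sized for a c-index of 0.8. That is right, so the 50% and 80% figures should not lead. The concern survives on the three-predictor scenario.

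The count of 14 is a reading. Analysing measures separately could mean separate models, and the collinearity check could remove some. Fourteen biomarkers plus age and sex already make 16 of the 17 planned candidates. That is fair, and the 7-term figures are the conservative end.

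A reader might infer that selection is no evidence at all, or that a selected biomarker becomes a compulsory test for patients. The document supports neither. A null biomarker is dropped in roughly 86-90% of studies, per-biomarker measures are reported, and the model is described as an aid to the clinician.

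**Conclusion.** The concern holds in a limited form. The selection rule does not limit false inclusion across the set, and no planned output shows which inclusions are stable. Selection alone is therefore weak, though not worthless, evidence for a given biomarker.

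With three true predictors, the named set also contains at least one useless biomarker in about 36-39% of studies (7 terms) or 68-79% (14 terms). Per null biomarker the rate is about 10-14%. If no biomarker had any effect, at least one would still be selected in about 50% or 80% of studies. These figures rest on 400 evaluable people (320 in one illustration), assumed effect sizes and correlations, and the two candidate counts.

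The prediction model stays usable. What needs repair is the statement of which biomarkers have been identified.

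**What to change.** Keep the stepwise model for the nomogram and make these changes:

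1. **Internal validation:** tabulate each biomarker's inclusion frequency over the 500 planned bootstrap selections. For CSF and MRI, also give the frequency with which any measure of that modality is selected, because correlated measures replace one another.
2. **Sensitivity analysis:** report which biomarkers are selected at each alternative threshold, by AIC and by LASSO, besides comparing performance.
3. **Statistical model and variable selection:** base both the word 'identified' and the check for negligible biomarkers on an inclusion-frequency criterion fixed in advance. Call the other selected biomarkers 'in the model, not established'.
4. **Model presentation and risk groups:** label final-model p-values and confidence intervals as not adjusted for selection.

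The level of the criterion matters. For a single term, treating the bootstrap z as normal around the observed z, the inclusion frequency is about Φ(|z| − 1.645). A frequency of 50% then means |z| = 1.645 (p = 0.10), no stricter than the present rule. A frequency of 80% means |z| = 2.49 (p = 0.013), and 90% means |z| = 2.93 (p = 0.0034), close to 0.05/14 = 0.0036. This is a guide under a simple approximation; the sponsor should set the level before analysis.

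A joint likelihood ratio test of all biomarkers over the clinical core could be added at no real cost, but it guards only against the case that none adds anything. At the planned R² the total likelihood ratio statistic is about −400·ln(1 − 0.31) = 148. If biomarkers carried a quarter of it (an assumption), 37 would exceed the 5% critical value of 23.7 on 14 df. The test would then usually reject and leave the composition of the set as uncertain as before.

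The cost is SAP wording and tables from computations already planned. The downside is that a weakly predictive biomarker may sit in the nomogram without being declared established.
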